## Abstract

**Background:**

Policy implementation remains an under researched area in most low and middle income countries and it is not surprising that several policies are implemented without a systematic follow up of why and how they are working or failing. This study is part of a larger project called Supporting Policy Engagement for Evidence-based Decisions (SPEED) for Universal Health Coverage in Uganda. It seeks to support policymakers monitor the implementation of vital programmes for the realisation of policy goals for Universal Health Coverage. A Policy Implementation Barometer (PIB) is proposed as a mechanism to provide feedback to the decision makers about the implementation of a selected set of policy programmes at various implementation levels (macro, meso and micro level). The main objective is to establish the extent of implementation of malaria, family planning and emergency obstetric care policies in Uganda and use these results to support stakeholder engagements for corrective action. This is the first PIB survey of the three planned surveys and its specific objectives include: assessment of the perceived appropriateness of implementation programmes to the identified policy problems; determination of enablers and constraints to implementation of the policies; comparison of on-line and face-to-face administration of the PIB questionnaire among target respondents; and documentation of stakeholder responses to PIB findings with regard to corrective actions for implementation.

**Methods/Design:**

The PIB will be a descriptive and analytical study employing mixed methods in which both quantitative and qualitative data will be systematically collected and analysed. The first wave will focus on 10 districts and primary data will be collected through interviews. The study seeks to interview 570 respondents of which 120 will be selected at national level with 40 based on each of the three policy domains, 200 from 10 randomly selected districts, and 250 from 50 facilities. Half of the respondents at each level will be randomly assigned to either face-to-face or on-line interviews. An integrated questionnaire for these interviews will collect both quantitative data through Likert scale-type questions, and qualitative data through open-ended questions. And finally focused dialogues will be conducted with selected stakeholders for feedback on the PIB findings. Secondary data will be collected using data extraction tools for performance statistics.

**Discussion:**

It is anticipated that the PIB findings and more importantly, the focused dialogues with relevant stakeholders, that will be convened to discuss the findings and establish corrective actions, will enhance uptake of results and effective health policy implementation towards universal health coverage in Uganda.

## Background

Policy implementation remains an under researched area in most countries and it is not surprising that several policies are implemented without a systematic follow up of why and how they are working or failing [1, 2]. It is for this reason that a project entitled “Supporting Policy Engagement for Evidence-based Decisions (SPEED) for Universal Health Coverage (UHC) in Uganda” was launched by the School of Public Health at Makerere University (MakSPH) in 2015. The overall objective of SPEED Project is to strengthen capacity for policy analysis, implementation monitoring and analysis of impact and thereby contribute to accelerating progress towards UHC in Uganda. This paper describes the proposed Policy Implementation Barometer (PIB) survey which is a mechanism to reveal gaps in policy implementation and thereby provide feedback to the decision makers about the implementation of a selected set of policy programmes for UHC. The feedback mechanism will include policy engagements to foster corrective action in areas where such is required. The SPEED project seeks to conduct 3 barometer surveys over its 5 year life span (2015–2020). Lessons from the first wave will advise the implementation of the policies, hence a second barometer survey using the same tools and approach will be conducted in the third years to evaluate progress and change in the implementation of the policies. Finally, the last barometer wave will be conducted in the fifth year, which is the final year of the project. By using the same tools and methods, this evaluation will detect the overall outcomes of the project.

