### Criteria for choosing policies to assess

There are many health policies in Uganda but this barometer will focus on selected priority policies for assessment in different phases or waves (See Table 2). The first wave of the barometer will focus on policies related to family planning, emergence obstetric care and malaria policies. Policies to assess were selected based on the criteria described below. In subsequent barometers (in year 3 and 5) policies to assess will also depend on consultation with stakeholders which include the Ministry of Health and government using the same criteria as well as the experience of the first round assessment.

**Table 2 Tab2:** Potential Polices for the Barometer

To ensure coverage of the whole health value chain, policies will be selected on the basis of their position in the value chain: (A) Prevention, (B) Treatment, (C) Follow up.
1) HIV policies
- Prevention of HIV e.g. ABC, PMTCT, etc.
- Treatment of HIV patients e.g. ART policies over time
- Follow up policies e.g. management of chronic illnesses, financing, management
2) Malaria policies
- Prevention of malaria policies e.g. insecticide-treated nets (ITNs) and Insecticide Residual Spraying (IRS)
- Treatment of malaria policies e.g. Antimalarial drug policies
- Follow up policies e.g. financing, management
3) Maternal mortality policies
- Prevention of maternal mortality e.g. maternal mortality reviews
- Treatment of pregnant patients e.g. Emergency obstetric care
- Follow up policies e.g. Policy on skilled birth attendance, financing, management
4) Family Planning
- Prevention of unplanned pregnancies e.g. contraceptive security
- Treatment of involuntary pregnant patients e.g. counselling, reproductive rights awareness
- Follow up policies e.g. service delivery and access, financing, management and stewardship
5) Child Health
- Prevention of child illness e.g. immunisation
- Treatment of child patients e.g. facilities, EPI
-Follow up policies e.g. Integrated Community Case Management (ICCM), financing, management

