### Study design

There will be three PIB waves. The first wave is the initial situation analysis survey which will assist the implementation of policies in the project’s lifespan. The second wave will be conducted in the third year of the project and the last wave will be final evaluation. Data collection will utilise the same tools and approaches in order to capture any changes hence, this PIB will be a longitudinal survey where both qualitative and quantitative data collection methods will be employed. The PIB study will be descriptive and analytical by focusing on selected policy cases with multiple assessment domains as outlined in Fig. 2.

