##### Quantitative data

The likert scale-type options will be used for key measures of implementation status. The three questionnaires covering the three policy domains of family planning, malaria and emergence obstetric care (annexes 1, 2 and 3) are structured to include issues of policy resources, policy standards, implementation processes and other contextual factors that mediate policy implementation, which are further summarised in Table 4 as a framework for organising the assessment of the policy domains. Each questionnaire has six modules and addresses objectives 1 to 3. The first module is about policy specific details i.e. the policy objectives, and related programmes and plans that guide the implementation. The programme activities were used to generate six generic modules for assessment in Fig. 2. In the first module, all the selected policies will be assessed on the basis of their unique policy aspects.

**Table 4 Tab4:** Framework for organizing the assessment domains for the- first wave of Policy Implementation Barometer

All Policy domains	Level of analysis	Policy resources (inputs)	Policy standards (process)	PIB indicator categories	Data sources
1. Family Planning 2. Malaria 3. Emergence obstetric care	Macro level	Availability of: • financial resources; • human resources (admin and technical staff); • other resources (equipment, supplies, medicines, etc.); • implementing agencies	Availability of: • regulations, • technical guidelines, • Standard Operating Procedures (SOPs); • Communication plan; • Enforcement mechanisms (normative, remunerative or coercive); • Policy champion; • Political resources (oversight committees, etc.); • Reporting structures and mechanisms	• Resources and services indicators • Community engagement indicators • Integration and responsiveness indicators • Family planning indicators • Malaria program coverage indicator *Emergency obstetric care* • Emergency obstetric care indicators • Policy champion; • Political resources (oversight committees, etc.); • Reporting structures and mechanisms	• Documents review • Key informant interviews • Interviews with implementers (all levels) • Secondary data (studies, surveys, routine health information, etc.
	Meso level	Same as above	Same as above	Same as above	Interviews Routine data
	Micro level	Facility level data - similar to the above	Facility level guidelines, SOPs, etc.	Facility level	Interviews Routine data

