For objective 5, we plan to learn from the process of dissemination of the PIB findings. The main methods of data collection will involve the active documentation of stakeholder reactions and responses to the findings. The questions they ask about the finding and the ideas they propose about PIB and about corrective actions to improve implementation of the policy programmes. We aim to organise 2–3 dissemination meetings, and 2–3 focused dialogues with sub-groups of stakeholders on key issues that emerge from the PIB. We will use a structured narrative to capture the main aspects of responses to the PIB findings. In cases in which dissemination happens using mass media (radio, TV), we will also note the comments and questions raised and or the proposed ideas from the media/public. These will be analysed and used to improve the PIB tool and to produce an “ideas brief” that will complement the barometer findings. The brief will be shared with the target group and also help in interpreting findings or making plausible recommendations.

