#### Questionnaire administration – On-line and face-to-face interviews

Through the two identified approaches, we seek to compare the on-line and face-to-face administration of the PIB questionnaires among the target groups. The purpose is to find the most effective way to interview respondents at the national, district and facility levels for the PIB. To inform future barometer surveys and to generate panel data to track trends in the key implementation domains, we will compare response rates, interview completeness and costs between on-line and face-to-face. A pool of respondents and their telephone contact at each level (national, district and facility) will be generated. From Table 3 half of the respondents will be assigned to either face-to-face or on-line interviews. Those that are assigned to fill on-line questionnaires will be requested to provide email addresses so that they can be invited to participate in the study. Within the email, a web-link to the survey will be provided. The survey will be hosted on the MakSPH server. To compensate respondents for the data and connectivity costs of filling the survey, a token of appreciation will be provided.

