## Ethical considerations

All respondents to the study will sign consent forms that clearly indicate how confidentiality will be protected in the study. No names will be recorded and all participants will be coded (anonymised) before analysis and reporting of results. No one will be forced to participate and refusals will be recorded as such. The phone contacts of the participants will not be shared with others outside of this study and will only be used for delivery of the survey. Phone contacts and all identifiers (such as titles, office names, etc.) will be will be stripped off the data to avoid tracing responses to a particular interviewee. Although a token of appreciation €10.0 will be provided to on-line interviewees, this is to compensate for the cost of data bundles that will be used by the respondents while responding to the survey. This token payment will not be used to coerce the respondents – although it will be offered at the point when the respondent terminates the interview. The phone number to receive this token will be provided at the point of exit from the online survey. These phone numbers will be used only for paying the token and not linked to the data a respondent has provided during the survey.

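### Later waves are said to measure change in the same policies and to detect the project's outcomes, but the policies may be re-chosen and the project has no comparator

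*Protocol article*

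**What the plan says.** On how the policies are carried out, the Background section describes "a second barometer survey using the same tools and approach will be conducted in the third years to evaluate progress and change". Of the final wave, in year five, it says: "By using the same tools and methods, this evaluation will detect the overall outcomes of the project". The Study design section takes the longitudinal label from the constancy of the instruments: "Data collection will utilise the same tools and approaches in order to capture any changes hence, this PIB will be a longitudinal survey".

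The section on criteria for choosing policies says: "In subsequent barometers (in year 3 and 5) policies to assess will also depend on consultation with stakeholders". It adds that the same selection criteria and the experience of the first round will be used. The Quantitative data section ties the instruments to the wave 1 policies ("The three questionnaires covering the three policy domains of family planning, malaria and emergence obstetric care"). It also says that the first module covers what is particular to each policy, and that modules generic across policies exist.

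The section on questionnaire administration gives one aim as "to generate panel data to track trends in the key implementation domains". Under Ethical considerations, participants are coded, and contacts and other identifiers are to be "stripped off the data to avoid tracing responses to a particular interviewee".

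The At district level section lists the selection criteria, names the ten districts and randomises them to on-line or face-to-face interview. No control districts, control policies or other counterfactual for the project are described.

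**The concern.** Two promises depend on features that the design does not secure.

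The first is change measured with constant tools. If the set of policies can move between waves, so can the policy-specific part of the tool, and the trend for any policy that moves is lost. A baseline not taken in wave 1 cannot be recovered in year 3.

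The second is detection of the project's outcomes. A before–after series without a comparator cannot separate the project from everything else that changed over the same years. A reader of the final report could take an improvement as the project's result when the data do not show that.

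A smaller matter is the panel. The article wants panel data but does not say what the panel unit is, or how waves will be linked once identifiers are removed.

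**Working it through.** **Stated figure.** The only number that bears on this is the sample size in Table 3: 120 national + 200 district + 250 facility = 570, which reproduces. The article gives no detectable change, SD, between-wave correlation or intraclass correlation. The calculations below are therefore illustrations. They assume SD = 1, two-sided 5% level, 80% power, independent respondents, and wave 1 numbers repeated in later waves.

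**1. Same tools against open policies.**
- Background and Study design: change is measurable because the tools stay the same.
- Criteria for choosing policies: the policies for years 3 and 5 are not fixed.
- Quantitative data: one questionnaire per policy domain, with policy-specific content in the first module.

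It follows that a change of policy changes at least the policy-specific part of the tool. The plan to collect stakeholder reactions to the findings points the same way ("These will be analysed and used to improve the PIB tool"), although the point does not depend on it.

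Size at national level, where Table 3 gives 40 respondents per policy domain. The minimum detectable change in a score pooled over the retained policies, with unlinked waves, is (1.960 + 0.842) × √(2/n):
- three policies retained, n = 120: 0.36 SD
- two retained, n = 80: 0.44 SD
- one retained, n = 40: 0.63 SD
- none retained: no policy-specific comparison

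**2. Outcome claim against no comparator.** The expected wave-to-wave change is the project effect plus background drift. One series gives one equation with two unknowns, whatever the sample size. The only randomised contrast is interview mode, which says nothing about the project.

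The chance that drift alone produces a significant change when the project effect is zero, using SE = √(2/570) = 0.059 SD:
- assumed drift 0.1 SD: 0.39
- assumed drift 0.2 SD: 0.92
- assumed drift 0.3 SD: above 0.99

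Clustering by district and facility would raise the SE and lower these probabilities, but would leave the bias as it is. The district criteria add two rival explanations. Choosing from the top and bottom of a league table invites regression to the mean in district-level change. Choosing districts where the investigators' institution already works brings in concurrent activities.

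**3. Linking.** With unlinked waves the variance of a change is 2σ²/n. With the same units linked it is 2σ²(1−ρ)/n. The ratio is 1/(1−ρ):
- ρ = 0.3: 1/0.7 = 1.4
- ρ = 0.5: 1/0.5 = 2.0
- ρ = 0.7: 1/0.3 = 3.3

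At n = 570 the detectable change is 0.166 SD unlinked, against 0.139, 0.117 and 0.091 SD linked. These ρ values are assumed. The formula ignores clustering and assumes that every unit is re-interviewed, so turnover over two to four years would reduce the gain.

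**The case against.** The article is chiefly the protocol of the first wave. None of its five objectives concerns change between waves or the effect of the project, and the study calls itself descriptive and analytical. The outcome claim is one sentence in the Background, and no causal analysis is described. This stands as a limit on the consequences: no wave 1 result depends on the claim. It does not remove the inconsistency, because the article itself makes the longitudinal, panel and outcome statements. They are not details left to a fuller document.

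Three stronger readings are tempting, and the article does not support them.
- A reader might infer that the policies will be replaced, and that replacing one of three loses a third of the content. The text permits re-choice but does not announce it, and generic modules could still be compared.
- A reader might infer that stripping identifiers makes it impossible to match facilities or posts. The text says that participants are coded and that identifiers come off the data. It does not exclude a separately held key or facility codes, and it does not say that the individual is the panel unit. The ten districts are named, so a district series is clearly possible.
- A reader might infer that failing to link doubles the variance. That follows only from one assumed correlation, with independence and full re-interview.

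It could also be said that routine data from other districts supply a comparator. The Study limitations section offers secondary data to offset limited coverage, not as a control. Nor could they restore attribution, since the project also engages national policymakers and other districts are exposed to that work.

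**Conclusion.** The point holds on two counts. The promise of constant tools for the same policies conflicts with the freedom to re-choose policies in years 3 and 5. The claim to detect the project's overall outcomes states a property that the design lacks. If a policy changes, its policy-specific trend is lost entirely, and only generic scores might carry over. On attribution, the project effect is not identified at any sample size. The probabilities of 0.39 to above 0.99 show how readily drift would look like a result, under assumed drifts of 0.1 to 0.3 SD and no clustering.

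The panel question is a matter for clarification, not a contradiction. The gain from linking, a variance ratio of about 1.4 to 3.3 for an assumed ρ of 0.3 to 0.7, is illustrative only. Describing change over time remains legitimate, and wave 1 stands as planned. The change is still worth making, because the core content and the means of linking have to be settled at wave 1.

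**What to change.** 1. In the section on criteria for choosing policies, state that malaria, family planning and emergency obstetric care, in the same ten districts, form a fixed core in all three waves, and that policies chosen later by stakeholders are additions. Cost: longer questionnaires in later waves if policies are added.
2. In the Background, replace the claim about detecting the project's outcomes with a statement that the waves describe change in implementation over the project period. Any comparison with other districts in the routine health information data should be labelled descriptive context only, because the project also works nationally. Cost: a more modest claim, and some analysis if that comparison is made.
3. Under Ethical considerations, clarify that the participant code retains district, facility and post through a separately held key, so that the intended panel data can be built without identifiers in the analysis file. Cost: ethics wording and secure storage of the key.

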## Purpose

Uganda has developed several acclaimed health policies to transform the wellbeing of its population. However, the intended results have not always been achieved due to inadequate implementation [3]. The identification of policy implementation failures and suboptimal performance through monitoring and accountability for policy implementation is mostly downward looking – mostly identifying frontline failings at service delivery levels. There is limited research and tools to monitor upstream actions (e.g. financing, partnerships and support systems) that are vital to the performance of frontline functions. This partly arises from the result-orientation in research funding and methodologies that are well established for the downstream outcomes and less well tuned for upstream and mid-level actions. Upstream monitoring is predominantly relational and process-oriented with fewer research tools to make meaning of the complex relationships that underlie up-stream functions. The health system research agenda has brought to the fore processes that support service delivery [4]. Once a policy is passed, there are often weak mechanisms to provide systematic feedback to the decision makers about implementation progress [1, 2]. Where it exists, it is often about what frontline actors should do to improve policy outcomes but less focused on the upstream actions that support implementation processes that may constrain implementation such as organizational architecture and partnerships, workforce capabilities, costs and financing, mobilization and compliance of policy beneficiaries. There are few tools that allow upstream policy makers and policy advocates to monitor implementation and to mobilize appropriate and continued policy support during the implementation phase.

There is limited research that tracks the implementation phase of policies for the benefit of informing corrective actions [1, 2]. This gap manifests in delayed corrective actions for policy implementation processes or gradual abandonment of policies that would otherwise transform the health and welfare of communities. Although some programme monitoring tools exist, these mostly serve a technocratic objective, mostly organised on the basis of project silos and internal indicators of project management. Evidence emerging from HIV programmes show that active implementation tracking of project indicators has a tendency to divert the health systems capabilities towards a couple of projects to the neglect of other vital policy programmes [5].

The specific objectives of the PIB study are (1) To assess the perceived appropriateness of policy programmes implemented to address identified policy problems (e.g. policy goals, strategies, standards and processes of decision making); (2) To assess, using priority parameters, the extent to which the prerequisites for implementation are established (e.g. awareness of policy objectives, resources provision, network of role bearers, community demand, policy champions); (3) To determine the enablers and constraints to implementation of the selected policies (e.g. workforce, finance, and medicines and the interdependencies of action network); (4) To compare on-line and face-to-face administration of the PIB questionnaire among target respondents (ease of access, response rate, costs); and (5) To document stakeholder responses to PIB findings with regards to policy implementation, awareness and actions. This will include dialogue on content such as implications and recommendation, actionable findings and role accountability collaborative actions.

